### Data collection

The data collection will be at three time points the first will be at baseline (T0), the second will be immediately after the 12-week intervention (T1) while the third will be three months after the intervention (T2). Details in Table 1. The data collection will employ a mixed methods approach including:(i)A desk review of relevant state and national NCDs prevention policies and guidelines on physical activity and an assessment of the level of coherence of the School Health Promotion policy with these policies. Other documents which will be reviewed include the Physical Health Education curriculum and school timetable to assess the opportunities for PA during school hours. The policies which regulate the construction of schools will also be reviewed to assess the extent to which these documents regulates or influences the built environment and physical activity levels in school.(ii)Physical and Health Education Teachers will complete the School Physical Activity Policy Assessment tool (S-PAPA) – a standardised semi-structured tool which assesses physical education, recess and other physical activity opportunities before, during and after school [31]. For this study, only two components will be assessed - physical education and recess. Scores on the S-PAPA tool will be tabulated based on policies and practices identified as being related to children’s physical activity during school [32, 33]. Total point scores will also be either median-split into high- and low or stratified by percentile for analysis [34].(iii) Focus Group Discussions and In-depth interviews will be held with teachers and school principals respectively to assess their opinion about social norms and support and the extent of implementation of physical activity policies and programmes in schools, level of funding, and the frequency of engagement in structured physical activity. Observations will be conducted to document facilities for physical activity in the schools using the Sport, Physical Activity and Eating behaviour: Environmental Determinants in Young people (SPEEDY) checklist. The SPEEDY checklist measures the built environment of schools and can be scored to quantify environmental support for physical activity [35]. The checklist assesses school-level environmental variables such as *Walking Provision, Cycling Provision, Aesthetics, Sport and facility provision, Other facility and Design of the school grounds* [36] The scores from each of the key variables will be dichotomised into low and high based on percentiles, and the school physical activity suitability index will be computed [36, 37].(iv) A cross sectional survey will be conducted among the students using an adapted version of the *Physical Activity Questionnaire for Adolescents (PAQ-A)* [38] to generate self-reported data on the level of physical activity among young people. The PAQ-A is a self-administered, 7-day recall instrument. It was developed to assess general levels of physical activity for high school students approximately 13 to 19 years of age. It assesses the frequency of participation in physical activity during spare time, physical education period, lunchtime, after school, in the evenings and on weekends. A summary of the physical activity score is generated from the mean of 8 items, and ranges from 1 to 5, with higher scores indicating more frequent participation in physical activity [38]). The physical activity levels will be categorised into three; low physical activity level will be those who score between 1 to 1.9 while moderate and high physical activity levels will be those who score between 2 to 3.9 and 4 to 5 respectively [13]. For some statistical analyses, the self-reported physical activity level will be treated as a continuous variable. In a study to establish the convergent validity of the PAQ-A, the instrument was found to be significantly correlated to all self-report measures (including activity rating, *r* = 0.73; Leisure Time Exercise Questionnaire, *r* = 0.57; and 7-day physical activity recall interview, *r* = 0.59) [39]. The survey will also assess the frequency of engagement in structured physical activity from two time points (baseline and follow up) as the primary outcome measure. Based on the theory of Planned Behaviours which is the theoretical framework guiding this intervention, other variables which will be incorporated into the Physical Activity Questionnaire for Adolescents (PAQ-A) are the measures for attitude, subjective norms, perceived behavioural control and self-efficacy. A research tool which was theoretically derived by Motl et al., 2000 based on Theory of Reasoned Action (TRA) and Planned Behaviour (TPB) and Social-Cognitive Theory (SCT) will be used to assess the social-cognitive factors among this young people. This questionnaire has been tested and evidence provided for its factorial validity as a unidimensional measure of attitudes, subjective norms, perceived behavioural control and self-efficacy about physical activity among adolescent girls [40]. The core variables i.e. *knowledge of health benefits of physical activity, attitude, subjective norms, perceived behavioural control and self-efficacy about physical activity* will be analysed by scoring and summing up all question items and cut-offs will be determined using percentiles.The survey will be complemented with focus group discussions to assess their opinions about the individual, social, community, institutional and policy factors which influences the physical activity behaviours of young people.(v)Anthropometric and other physical measurements (body-mass-index for age, waist-to-hip ratio, blood pressure) will be documented. Anthropometric measurements will be taken twice and averaged; for discrepancy >10%, a third measurement will be taken. The height and weight will be assessed using standard anthropometric procedures. Height will be measured using a portable height meter/stadiometer. Students will be asked to take off their shoes and stand with their back to the portable height meter/stadiometer. The sliding bar will be lowered and pressed flat on the head and recorded to the nearest centimeter. Body weight will be measured using a digital scale and weight will be recorded to the nearest gram. Age -and sex -specific prevalence of overweight and obesity will be determined by the body-mass- index for age Z scores using the criteria defined by the World Health Organisation (WHO). According to the WHO cut off points; overweight is considered to be > + 1SD (equivalent to BMI 25 kg/m2 at 19 years), Obesity: > + 2SD (equivalent to BMI 30 kg/m2 at 19 years), Thinness: <-2SD, Severe thinness: < −3SD and Normal: > −1 to < +1 SD. Standard deviations (Z-scores) will be computed using the World Health Organisation (WHO) reference population, 2007 soft ware (Anthropometric Software Program, Version 1.0.4 [41]. Blood pressure will be measured and the mean of three measurements will be recorded. Referrals will be initiated for children whose blood pressure exceeds the 95th percentile for age. Waist circumference will be measured to the nearest 0.1 cm horizontally at the narrowest point between the lower end of the rib cage and iliac crest. Hip circumference will be measured to the nearest 0.1 cm, at the greatest horizontal circumference below the iliac crest at the level of greater trochanter. Waist hip ratio will be obtained as waist circumference/hip circumference.The fitness level of the adolescents will be measured using the 20-m shuttle run test (20-mSRT) also known as the multi-stage fitness test. The 20-mSRT is the most widely used field-based test for aerobic fitness in young people and UK percentile data and health-related cut points are available [42]. A systematic review recently concluded that the 20-mSRT is the most reliable and valid field based method to estimate aerobic fitness in young people [43]. Performance in the 20-mSRT is typically expressed as laps, levels or distance completed. The 20mSRT estimates the cardiorespiratory fitness (aerobic capacity). Children run back and forth between two lines 20-m apart following beep signals played from a pre-recorded CD. The pace of the test is ramped such that running speed increases by 0.5 km/h each minute or period. The test is finished when the child stops owing to fatigue or when he/she does not reach the line in time with the audio signal on two consecutive occasions [44]. The last completed run indicates the final result of the test. The physical fitness data will be analysed and used as continuous variables and an increase in test results will indicate higher physical fitness [45].(vi) Step count will be recorded using a pedometer. During the data collection process, 100 students (10% of the sample) will be asked to wear a Yamax SW200 Step Digi-Walker pedometer on their right hand for seven consecutive days, except during sleep and water based activities. Text messages/phone calls will be made daily as reminders to ensure compliance. The pedometers will be sealed with a sticker or cable to prevent reactivity i.e. a situation where individual change their normal activity pattern as a result of being monitored.The pedometers will be worn daily for seven days with a minimum of 4 valid days. Step counts of less than 1000 steps per day and greater than 30,000 steps per day will be treated as missing data [46]. Step count of 10,000 to 11,700 and over will be recorded as achieving the daily recommended levels of 60 min of MVPA in adolescents [47].

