### Secondary outcome measures

Secondary measures which will be documented are fitness levels, anthropometric and physical measurements, knowledge of the *health benefits of physical activity, attitude, self efficacy, perceived behavioural control and intention, Social Norms, Social support, policy or programme changes* on PA. Details in Table 2.

**Table 2 Tab2:** Data elements to be collected, study timepoints (T0, T1, T2) target groups

Description of outcome measures	Method	Type of variable	Timing	Target group
Demographic characteristics, Socio-economic status	Questionnaire	Ordered categorical	T_0_ T_1_ T_2_	Adolescents
Knowledge, attitude, beliefs on nutrition and PA	Questionnaire	Ordered categorical	T_0_ T_1_ T_2_	Adolescents
Self-reported physical activity levels	Physical Activity Questionnaire (PAQ –A) for adolescents	Continuos	T_0_ T_1_ T_2_	Adolescents
		Ordered categorical		
PA Self efficacy	Questionnaire	Ordered categorical	T_0_ T_1_ T_2_	Adolescents
Perceived behavioural control and intention	Questionnaire	Ordered categorical	T_0_ T_1_ T_2_	Adolescents
Fitness level measured using the 20-mSRT	20-mSRT	Ordered categorical	T_0_ T_1_ T_2_	Adolescents
Step count (average steps/day)	Pedometers	Continuous	T_0_ T_1_ T_2_	Adolescents
Anthropometric and Physical assessments (BP, Ht, Wgt, BMI)	Brief physical assessment	Continuous	T_0_ T_1_ T_2_	Adolescents
Social Norms and Social support,	Questionnaire	Ordered categorical	T_0_ T_1_ T_2_	Adolescents, Teachers, School Heads
Built environment	Observation and checklist	Ordered categorical	T_0_	School Environment
Policy or programme changes	Key Informant interviews	Qualitative	T_0_ T_1_ T_2_	School Heads, Officials of Govt. and Ministries Policy Makers,

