#### Data management and statistical analysis

Serial numbers will be assigned to the questionnaires for easy identification and recall of the instrument and these will be stored in a place safe. A coding guide will be developed and sections of the tools which are open ended will be coded before data entry. The data will be cleaned to identify and correct all errors. The quantitative data will be analyzed using STATA version 13.

There are two key primary outcome variables specifically step count measured with pedometers which is a continuous outcome variable and self-reported physical activity level which can be a continuos or ordered categorical variable, details in Table 4.

**Table 4 Tab4:** Description of outcome Measures

	Description of outcome measures	Type of Variable
Primary Outcome Measures	Self-reported physical activity score/levels	Continuous
		Ordered categorical
	Step count (average steps/day)	Continuous
Secondary Outcome Measures	Anthropometric Measurements (measured using body mass index)	Ordered categorical
	Fitness level measured using the 20-mSRT	Ordered categorical
	Knowledge of the health benefits of physical activity	Ordered categorical
	Attitude toward Physical activity	Ordered categorical
	Self efficacy	Ordered categorical
	Perceived behavioural control and intention	Ordered categorical
	Social Norms and Social support,	Ordered categorical
	Policy or programme changes	Qualitative

At baseline, bivariate analysis (cross tabulation) will be used to compare the differences in proportions of the primary and secondary outcome measures of the experimental and control groups. Chi-square test (X^2^) will be used for significance testing of the self-reported physical activity levels (dependent ordered categorical variable) and other categorical independent variables while repeated measures ANOVA will be used for Step count (average steps/day). Based on data generated using bivariate analysis, all independent variables which are significant at 10% will be incorporated into the regression model.

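### The BMI-for-age classes are not exhaustive: Z-scores from -2 to -1, and exactly +1, have no category, although Table 4 treats BMI as an ordered categorical outcome

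*Protocol article*

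**What the plan says.** Item (v) of the protocol's Data collection section gives the purpose of the cut-offs: the "prevalence of overweight and obesity will be determined by the body-mass- index for age Z scores". It refers to WHO criteria and then lists five classes.

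- The middle class is written as "and Normal: > −1 to < +1 SD".
- On the lean side, the list has two nested classes, given as "Thinness: <-2SD, Severe thinness: < −3SD".
- On the heavy side, the first threshold reads "overweight is considered to be > + 1SD (equivalent to BMI 25 kg/m2 at 19 years". A second class, obesity, starts above +2 SD and is nested within it.

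Each student's Z-score comes from the WHO 2007 reference software.

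The abstract names BMI-for-age as a secondary outcome. The two outcome tables give different variable types:

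- Table 4 (Data management and statistical analysis) has the row "Anthropometric Measurements (measured using body mass index", typed as ordered categorical.
- Table 2 (Secondary outcome measures) has the row "Anthropometric and Physical assessments (BP, Ht, Wgt, BMI", typed as continuous and measured at T0, T1 and T2.

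No other part of the protocol defines BMI categories.

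**The concern.** An ordered categorical outcome needs classes that cover every possible value once. Here the upper limit of the normal class meets the overweight cut-off at +1, but its lower limit stops a full SD above the thinness cut-off. Someone coding the data by the stated rule has three choices for a student at Z = -1.5: leave the student uncoded, call the student normal, or invent a class. The protocol does not choose.

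The block affected is on the lean side and may be as large as the whole overweight-plus-obese group. If uncoded students were treated as missing, two things would follow. The class percentages would be taken over too small a denominator. A student whose Z-score crossed -1 or -2 between waves would also gain or lose a category in the repeated-measures data.

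**Working it through.** **Coverage of the Z scale by the stated rule**

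| Z-score | Class as written |
|---|---|
| below -3 | severe thinness (also meets thinness) |
| -3 to just below -2 | thinness |
| **-2 to -1 inclusive** | **none** |
| just above -1 to just below +1 | normal |
| **exactly +1** | **none** |
| just above +1 to +2 | overweight |
| above +2 | obesity (also meets overweight) |

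**Share of the reference population.** The protocol gives no expected share per class, so there is no figure of its own to reproduce. Assume Z is standard normal in the reference itself:

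- Gap: Φ(-1) - Φ(-2) = 0.1359, or 13.6%; 0.1359 × 1,000 = about 136 students.
- Cross-check: thinness 2.28% + normal 68.27% + overweight and obesity 15.87% = 86.4%, leaving 13.6%.
- If normal ran from -2 to +1: Φ(1) - Φ(-2) = 0.819, so normal would hold 81.9% instead of 68.3%, and only boundary conventions would remain to be settled.

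**Share expected in this trial.** The inputs are the overweight and obesity prevalences in the Background: Oyo 8.8% and 1.2%, Benue 9.7% and 1.8%, Lagos 13.8% and 9.4%, Ondo 5.8% and 1.1%. Three assumptions are added: Z is normal with SD s, the quoted prevalences correspond to Z above +1, and s is 0.8 to 1.2. The mean is then μ = 1 - s × z(1 - p), where p is the proportion above +1, and the gap is Φ((-1 - μ)/s) - Φ((-2 - μ)/s).

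For Oyo with the two figures added, p = 0.10. At s = 1, μ = 1 - 1.28 = -0.28, and the gap is 19.3%.

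| Prevalence used | s = 0.8 | s = 1.0 | s = 1.2 |
|---|---|---|---|
| Oyo, added (10.0%) | 10.5% | 19.3% | 23.9% |
| Oyo, obese already within the 8.8% | 11.8% | 20.9% | 25.1% |
| Benue, added (11.5%) | 9.2% | 17.6% | 22.4% |
| Lagos, added (23.2%) | 3.7% | 9.1% | 13.7% |
| Ondo, added (6.9%) | 14.3% | 23.8% | 27.3% |

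The Oyo rows, together with the other states at s = 1, span about 9% to 25%. Crossing every state with every SD widens this to 3.7% (Lagos, s = 0.8) and, if Ondo's 5.8% already includes the obese, 28.6% (s = 1.2).

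**Effect if uncoded students were treated as missing.** In the reference population, overweight including obesity would read 15.87/86.41 = 18.4% instead of 15.9%. With the Oyo calibration at s = 1 it would read 10.0/(100 - 19.3) = 12.4% instead of 10.0%. With all measured students in the denominator there is no error.

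**The case against.** The strongest reply is that little is lost. Every measured student has a Z-score. The stated use of the cut-offs is the prevalence of overweight and obesity, and a student at -1.5 is plainly neither overweight, obese nor thin, so those prevalences can be computed on the full sample as the cut-offs stand. Table 2 already treats BMI as continuous. The list also reads as nested cut-offs more than as a five-way code, Table 4 does not say that its categories are these, and the normal limit may be a slip in transcribing the WHO criteria.

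Most of this stands, and it rules out three stronger readings that a reader might infer:

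- That these students are dropped from the outcome. No section says so.
- That the thinness, overweight and obesity denominators are wrong. They are wrong only if uncoded students are removed.
- That 14% is a minimum. It is the reference-population value; a Lagos-type distribution, or a smaller SD, gives less. Nor is a mean Z of -1.0, which would put 34% in the gap, compatible with the quoted data: at SD 1 only 2.3% would then exceed +1, against about 9% to 10% in the Oyo study.

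The reply does not close the gap. Table 2 contradicts Table 4 and so does not cure it, and Table 4 sits in the statistical analysis section. A slip in a stated coding rule is still the rule an analyst would follow. Nor is this detail that a fuller plan would normally supply: the article states the cut-offs itself and states them incompletely.

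**Conclusion.** The point holds as a definition gap of limited reach. The listed classes omit Z from -2 to -1 inclusive and Z exactly +1, and these are the only categories available for the ordered categorical BMI outcome in Table 4. The share affected is 13.6% of a standard normal reference, and roughly 9% to 25% when calibrated to the prevalences the protocol quotes. That range rests on normality, on an assumed SD, and on those studies having used comparable cut-offs; the most extreme combinations reach about 4% and 29%.

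The certain damage is to the normal class and to the ordered categorical form of one secondary outcome. A continuous BMI analysis, the primary outcomes and the sample size are not affected. The disagreement between Tables 2 and 4 on variable type is part of the same problem, because it decides whether the gap reaches the analysis at all.

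**What to change.** 1. Rewrite the class list so that it is exhaustive and mutually exclusive, and check it against the WHO criteria the protocol cites. The protocol's own neighbouring cut-offs leave -2 to +1 inclusive as normal. That gives severe thinness below -3, thinness from -3 to below -2, normal from -2 to +1, overweight above +1 to +2, and obesity above +2. If the cited criteria contain a separate class between -2 and -1, add that class instead.
2. State that every student with a valid Z-score stays in the denominator of each prevalence.
3. Give BMI the same variable type in Tables 2 and 4. The better choice is BMI-for-age Z as the continuous secondary outcome in the planned multilevel mixed model, with the categories reported descriptively. This avoids losing information at the cut-offs and makes the effect estimate independent of them.

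The cost is a few lines in the protocol and the matching entries in the coding guide. No new measurements and no change to the sample size are needed.

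### Fitness and BMI are each given two scales of analysis, and the summed psychosocial scores are cut at unspecified percentiles; all should be continuous for the intervention-effect analysis

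*Protocol article*

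**What the plan says.** **Fitness.** Data collection, item (v), states: "The physical fitness data will be analysed and used as continuous variables and an increase in test results will indicate higher physical fitness". Table 2 (Secondary outcome measures) has the row "Fitness level measured using the 20-mSRT 20-mSRT Ordered categorical", and Table 4 (Data management and statistical analysis) has "Fitness level measured using the 20-mSRT Ordered categorical".

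**BMI.** Table 2 has "Anthropometric and Physical assessments (BP, Ht, Wgt, BMI) Brief physical assessment Continuous". Table 4 has "Anthropometric Measurements (measured using body mass index) Ordered categorical". Data collection, item (v), computes BMI-for-age z-scores and also lists WHO weight categories.

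**Psychosocial scores.** Data collection, item (iv), sums the items for knowledge, attitude, subjective norms, perceived behavioural control and self-efficacy, and adds that "cut-offs will be determined using percentiles". Tables 2 and 4 type these outcomes as ordered categorical.

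**Effect analysis.** The end of the statistical analysis section plans multilevel mixed-effects models for repeated measures with random effects for cities and schools. It does not say on which scale each secondary outcome enters them.

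**The concern.** The scale of an outcome decides whether the mixed model is linear or ordinal, and what its treatment effect means: a difference in mean result, or a shift between categories. Two analysts following this article could report different fitness or BMI results, and the choice could be made after the data are seen. Fitness is not incidental: the end of the Background and the Study research design section both name it, with physical activity, as something the intervention is meant to change.

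For the psychosocial scores, a summed score is reduced to a few groups before analysis, which gives up precision. The boundaries are also loosely fixed. No external norm is named, so percentiles of the trial's own sample are the natural reading, though the text does not say so. It also does not say whether the boundaries are set once or again at each of T0, T1 and T2.

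**Working it through.** **1. Is the double typing deliberate?** Self-reported physical activity is the one outcome that Tables 2 and 4 list as both continuous and ordered categorical, and the analysis section says it can be either. No such statement covers fitness or BMI.

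- Fitness: the text says continuous, both tables say ordered categorical. The text mentions that UK cut points exist but adopts none, so the categories are undefined.
- BMI: continuous in Table 2, ordered categorical in Table 4. The listed categories place normal between −1 and +1 SD and thinness below −2 SD, so a z-score between −2 and −1 has no label.

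**2. Precision lost, independent pupils.** The protocol gives no figure to reproduce. Assume a normal score and a small mean shift. The efficiency of a grouped score relative to the continuous score is

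E = Σ [φ(z_lower) − φ(z_upper)]² / p_group,

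summed over the groups, where φ is the normal density.

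- Median split: φ(0) = 0.3989, so E = 2 × 0.3989² / 0.5 = 0.637; loss 36%.
- Tertiles: cuts at ±0.431, φ = 0.3636, so E = 2 × 0.3636² / (1/3) + 0 = 0.793; loss 21%.
- Quartiles: φ(0.674) = 0.3178, so E = 2 × 0.3178² / 0.25 + 2 × (0.3989 − 0.3178)² / 0.25 = 0.861; loss 14%.
- One cut at the 75th percentile: E = 0.3178² / 0.75 + 0.3178² / 0.25 = 0.539; loss 46%.

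**3. Precision lost in the comparison of arms.** Schools are randomised, so the relevant comparison is between school means. Inputs: 1000 pupils in 22 schools, 1000 / 22 ≈ 45 per school, and a latent normal score with the stated ICC. For a continuous score the variance of a school mean is ICC + (1 − ICC)/45. For a median split, the covariance of two pupils' indicators is c = arcsin(ICC)/(2π), the variance of a school's proportion is c + (0.25 − c)/45, and the squared sensitivity to a shift is φ(0)² = 0.1592.

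Worked at ICC 0.05:
- c = 0.00796; proportion variance = 0.00796 + 0.24204/45 = 0.01334; information = 0.1592 / 0.01334 = 11.93.
- Continuous: 0.05 + 0.95/45 = 0.07111; information = 1 / 0.07111 = 14.06.
- Efficiency = 11.93 / 14.06 = 0.848; loss 15%.

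The same method for the other cases, with equally spaced category scores:

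| ICC | Median split | Tertiles | Quartiles | Cut at 75th percentile |
|---|---|---|---|---|
| 0 | 36% | 21% | 14% | 46% |
| 0.01 | 28% | 15% | 10% | 37% |
| 0.05 | 15% | 7.5% | 5% | 22% |
| 0.10 | 10% | 5% | 3% | 15% |
| 0.38 | 5% | 3% | 2% | 13% |

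The 0.38 is the protocol's sample-size value for physical activity. None is given for fitness, BMI or the psychosocial scores.

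**4. Recomputed cut-offs.** If the percentiles were taken afresh at each wave from both arms together, the pooled share in each category would be the same at every wave by construction, and overall change over time could not be seen. The arms could still differ in their shares, so the treatment contrast would remain.

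**The case against.** **All of these are secondary outcomes.** The sample-size calculation uses none of them, and the title names only physical activity. This stands and limits the weight of the point. A reader might infer that fitness is the title question; it is part of the stated aim, no more.

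**The two BMI rows may describe two forms of one measure.** Table 2's row, "Anthropometric and Physical assessments (BP, Ht, Wgt, BMI"), lists measured quantities, and Table 4 may mean the WHO classification of the z-score. The WHO cut-offs are external and fixed, so the worry about sample-based boundaries does not apply to BMI. This is a fair reading, but it still leaves the analysed form unstated.

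**The precision loss may be small.** A reader might infer that the plan discards a fifth to a third of the information. The documents do not support that as a fact: it assumes tertiles or a median split, normal scores and independent pupils, whereas the article fixes no cuts and randomises schools. Clustering shrinks the loss.

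**Details of cut-offs often sit in a fuller document, and ordinal mixed models exist.** Both are true. The missing percentile rule alone would not be a finding. What remains is a stated contradiction, and a stated categorisation where a better analysis costs almost nothing.

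**Conclusion.** The contradiction in fitness is plain on the page, and the analysed form of BMI is unsettled between the two tables. Cutting summed psychosocial scores at percentiles is a stated choice that loses precision for no evident gain. The size of that loss is an assumption, because neither the cuts nor the ICCs are given. For a median split or tertiles it runs from 36% and 21% with independent pupils down to 5% and 3% at an ICC of 0.38 with about 45 pupils per school.

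A reader might also infer that percentile cut-offs would erase change over time or the treatment effect. Nothing says they will be recomputed at each wave, and even then only overall change would be hidden. The point deserves correction before analysis, but it does not touch the primary outcomes or the sample size.

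**What to change.** In Tables 2 and 4, type the 20-mSRT result, the BMI-for-age z-score and the summed knowledge, attitude, norms, control and self-efficacy scores as continuous for the intervention-effect analysis, in line with the text on fitness. Analyse each with the multilevel mixed model already planned. Keep categories for description only: the WHO cut-offs for BMI, and percentile cut-offs fixed once at T0 for the psychosocial scores.

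The cost is table wording, and effect estimates that are less directly readable than shares of pupils in a category; the descriptive tables still supply those shares. No new data are needed.
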